### Sample size calculations

A power calculation was undertaken based on findings from a study by Gifford et al. [53], which used self-efficacy for controlling symptoms as the primary outcome measure. This study employed a symptom self-efficacy scale developed specifically for measuring the impact of self-management interventions for chronic diseases, and closely reflects the self-efficacy measure developed for use in evaluating the Positive Outlook program. Following an RCT aimed at evaluating the effectiveness of a self-management in men with symptomatic HIV or AIDS, Gifford et al. reported that self-efficacy for controlling HIV symptoms increased in the intervention group, and decreased in the control group (+4 versus -7; p = 0.02) [53]. Based on these findings, a sample size of 52 in each group was found to be adequate to identify a mean difference in score of 11 (assuming a standard deviation of 19.8), with 80% power and using a α = 0.05. The RCT would then require a total sample size of N = 104. If there appear to be any differences in baseline characteristics between groups, a regression model may be used to adjust for these. The general ‘rule of thumb’ is that a sample size of approximately 120 would be adequate to identify covariates which exhibit a moderate effect size power = 80%). Therefore the RCT will aim to recruit at least N = 120, requiring four rounds of randomisation of 30 participants. The research team believes this is a feasible number to achieve.

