### Pilot study

A pilot study to test the feasibility of the Positive Outlook program and to provide both formative and process evaluation was conducted in June 2012. Twelve participants were recruited from the target population for this pilot study through the Western Australian AIDS Council. Ten participants completed baseline assessments and were enrolled to participate in the seven week Positive Outlook program. One participant withdrew in week five due to personal issues. Data was collected from the remaining nine participants immediately following the intervention. Six of the nine participants were also interviewed about their experience of using the online program. Minor adjustments were made to the content and delivery of the intervention based on the results of the pilot study.

A second pilot study was launched on the 22^nd^ October, 2012. This pilot group was intended to be the first of the RCT, however it was decided that a few additional changes were required to improve the program prior to trial. Participants completed baseline data and were randomised into the intervention (n = 19) or the control group (n = 17). Two participants withdrew in week three. Data was collected from 21 participants at the conclusion of the intervention. The findings of the pilot studies will be reported elsewhere. Participation on the discussion boards was extremely limited for the intervention group. Engagement with the Action Plans was also limited. After discussions with the facilitators of the program, interviews with the participants themselves and discussion with the intervention team, we decided to include a “live chat” into future versions of the program. We believed that the program was too flexible and the delay in responses was acting as a barrier for participation for many of the participants. By facilitating a live chat, participants will have more accountability for participation and will potentially get more out of instant responses and the “virtual” conversation whilst still maintaining their anonymity.

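### The recruitment target of 120 absorbs at most 13.3% missing outcomes, while the trial's own randomised pilot had 41.7% missing, so 80% power is not supported unless retention is much better than in that pilot

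*Protocol article*

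**What the plan says.** All references are to the protocol article.

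**Sample size calculations.** The section states that "a sample size of 52 in each group was found to be adequate to identify a mean difference in score of 11". The inputs behind this are an SD of 19.8, power of 80% and alpha of 0.05, and the resulting total is 104. The total is then raised because baseline differences may need regression adjustment, and about 120 is said to be enough to identify covariates of moderate effect. The section concludes: "Therefore the RCT will aim to recruit at least N = 120, requiring four rounds of randomisation of 30 participants". It gives no expected loss rate and no allowance for missing outcomes, and neither does any other section.

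**Pilot study.** The second pilot was planned as the first group of the trial. Its men were "randomised into the intervention (n = 19) or the control group (n = 17"), that is, 36 in all. Two are said to have withdrawn in week three. At the end, "Data was collected from 21 participants at the conclusion of the intervention". Live chat was added to the programme afterwards. The first pilot, which was not randomised, enrolled ten men and obtained post-programme data from nine.

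**Data collection and Statistical analysis.** Outcomes are collected at the end of the intervention (or eight weeks after randomisation) and 12 weeks after the intervention. The analysis is ANCOVA at both times, on an intention-to-treat basis.

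**The concern.** A power calculation for a difference in means counts men whose outcome is observed. The plan computes that number and then raises it for a reason unrelated to missing data. The margin this happens to create is well below the proportion with missing data in the sponsor's own randomised pilot, which the same article reports a few sections earlier.

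What is at stake is how the result is read. Readers will judge the trial against the stated 80%. If retention resembles the second pilot, the chance of detecting an 11-point difference is materially lower, and a non-significant result carries less weight than the stated power suggests. The later time point is the more exposed of the two, because further men may stop responding in the 12 weeks after the programme.

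**Working it through.** **Inputs**

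- Difference 11, SD 19.8, power 80%, alpha 0.05, 52 per group, total 104, target 120 (Sample size calculations). Sidedness is not stated.
- Second pilot: 19 + 17 = 36 randomised, 21 with end-of-intervention data (Pilot study).
- First pilot: 10 enrolled, 9 with data (Pilot study).

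**1. Reproduce the plan's figure.** The standardised difference is 11/19.8 = 0.556. A two-sided, two-sample t-test at alpha 0.05 needs 51.8 per group, so 52, which gives power 80.1%. A one-sided test would need only 41 per group (normal approximation), so the calculation is two-sided. The plan's 52 and 104 are correct.

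**2. What 120 can absorb.** (120 − 104)/120 = 16/120 = 13.3%. With no loss, 60 per group gives 85.5% power.

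**3. What the pilots showed.**

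- Second pilot: 36 − 21 = 15 men without end-of-intervention data; 15/36 = 41.7%, exact 95% CI 25.5% to 59.2%. The lower limit is nearly twice 13.3%.
- Both pilots pooled: 21 + 9 = 30 of 36 + 10 = 46 with data, so 16/46 = 34.8% missing, exact 95% CI about 21% to 50%. This interval also lies above 13.3%.

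**4. Unadjusted power at N = 120.** The analysable number per group is 60 × (1 − loss). Power is for 11 points at SD 19.8, from the noncentral t.

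| Missing outcomes | Analysable per group | Power |
|---|---|---|
| 0% | 60 | 85.5% |
| 10% (first pilot) | 54 | 82% |
| 13.3% | 52 | 80% |
| 20% | 48 | 77% |
| 25.5% (lower limit, second pilot) | 44.7 | 74% |
| 30% | 42 | 71% |
| 34.8% (pooled pilots) | 39.1 | 68% |
| 41.7% (second pilot) | 35 | 63% |

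At 35 per group, the difference detectable with 80% power is about 13.5 points instead of 11. Ending with 104 analysable men at that loss would take 104/(1 − 15/36) = 178.3, so 179 recruits.

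**5. What ANCOVA could recover at 35 per group.** Let r be the correlation between baseline and post score. The article does not say which SD 19.8 is.

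- If it is the SD of the post score, the residual SD is 19.8 × √(1 − r²).
- If it is the SD of the change, the post-score SD is 19.8/√(2(1 − r)), and the residual SD becomes 19.8 × √((1 + r)/2).

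| r | Post-score SD: residual SD, power | Change-score SD: residual SD, power |
|---|---|---|
| 0.5 | 17.1, 75% | 17.1, 75% |
| 0.6 | 15.8, 82% | 17.7, 73% |

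Reaching 80% needs r of about 0.58 or more on the first reading, and about 0.34 or less on the second. The two readings move in opposite directions as r rises.

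**6. What a null result could exclude at 35 per group.** The standard error is 19.8 × √(2/35) = 4.73. With t(68) = 1.995, the 95% CI half-width is 9.4.

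**The case against.** The strongest reply is that nothing is miscalculated. The plan attaches 80% power to 104, which is right; 120 is a minimum target; and the 16 extra men act as an allowance whatever reason was given for them. That stands. The shortfall is conditional on loss above 13.3%, and a reader who infers that the trial is certain to miss 80% power goes further than the document allows.

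The second pilot is also an imperfect forecast. Live chat was added because of it, to raise participation, and the first pilot obtained data from nine of ten. Reminders by email, SMS and phone are described for the main trial, and the article does not say whether that pilot had them. These points weaken the forecast without removing it. Live chat reaches only the intervention group, the first pilot was small and had no control group, and no revised loss rate is given.

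A reader might call the 15 men lost. The article describes only two withdrawals; for the rest it is known only that they gave no end-of-intervention data. For power, that is what counts. An intention-to-treat approach does not create the missing outcomes.

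The unadjusted 63% is not the power of the planned ANCOVA, which could be higher. That also stands, but the article claims no such gain and states no correlation.

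A reader might further infer that a null trial of this size could not exclude an 11-point benefit. That does not follow. With 35 per group, an observed difference of zero has a 95% CI of −9.4 to +9.4, and any observed difference below about 1.6 (11 − 9.4) excludes 11. Lower power makes a true 11-point effect easier to miss; it does not mean that every null result is compatible with one.

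Finally, a journal article condenses the full protocol, where a retention assumption may exist. Here, however, the article sets out its reasoning for 120 explicitly, and that reasoning does not address the pilot figure it reports.

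**Conclusion.** The concern holds as a conditional one. The sample-size arithmetic is correct, but the target of 120 is not tied to any retention assumption and covers at most 13.3% missing outcomes. The trial's closest evidence, the randomised second pilot, had 41.7% missing at the first post-randomisation time point. Both the lower confidence limit of that figure (25.5%) and that of the two pilots pooled (about 21%) exceed 13.3%. The stated 80% is therefore not supported unless retention is much better than in that pilot.

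The unadjusted power is 77% at 20% loss, 71% at 30% and 63% at the second pilot's rate. These figures assume a two-sided t-test, equal groups, equal loss in both groups, and the plan's own difference and SD. ANCOVA could raise them by an amount that cannot be fixed without the correlation and the meaning of 19.8.

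**What to change.** Keep N = 120 and rewrite the sample-size paragraph so that it:

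1. says that 104 means men with outcome data;
2. no longer gives the covariate rule of thumb as the reason for 120;
3. states an expected loss rate at the end of the intervention and at the 12-week follow-up, justified against both pilots (21 of 36 and 9 of 10) and noting that live chat was added after the second;
4. gives the unadjusted power at N = 120 by loss: about 80% at 13%, 77% at 20%, 71% at 30% and 63% at 42%, with a detectable difference of about 13.5 points in the last case;
5. if a gain from ANCOVA is claimed, states the assumed baseline correlation and whether 19.8 is a post-score or a change-score SD.

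The cost is a rewritten paragraph and a less favourable stated power. It needs no extra participants and no change to the design or analysis. The Trial status section says that no trial data had been cleaned or analysed at submission, so the restatement could be made without knowledge of results.

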### Data collection

#### Quantitative data

Data will be collected online (via Survey Monkey) with the exception of the SF-12^®^ which the primary researcher (TM) will deliver via post or phone. Electronic questionnaires will be emailed to participants at three time points: baseline (Timepoint 1); immediately after the completion of the intervention or eight weeks post randomisation (Timepoint 2); and 12 weeks following the intervention (Timepoint 3). Demographic information will be collected at time one only and will include age, year of diagnosis, co existing conditions, relationship status, living situation and annual income. It is anticipated that data collection at each timepoint will take no longer than 45 minutes to complete. Participants will be given two weeks to submit completed follow up questionnaires. They will receive email, SMS and phone reminders as required. For a detailed flow chart on data collection, please see Figure 1.

**Figure 1 F1:**
[figure not shown]
Flow chart of Positive Outlook Study intervention process.

#### Primary outcome measures

##### 

**Patient Reported Outcomes Quality of Life-HIV (PROQOL-HIV)** The PROQOL-HIV was developed to measure the health related quality of life of PLHIV in the current HAART era [54]. The PROQOL-HIV demonstrates good convergent and discriminant validity and reliability (8% scaling success; Cronbach alphas 0.77-0.89) [55].

##### 

**Outcomes of health education: Health Education Impact Questionniare (heiQ)** The Health Education Impact Questionnaire (heiQ) will be used to evaluate the effectiveness of the program. The heiQ evaluates patient education and self-management programs for chronic illness [56]. It has demonstrated high construct validity ranging from 0.70 to 0.83 for each of the dimensions [57].

##### 

**Domain specific self-efficacy: Positive Outlook Self-efficacy Scale** The Positive Outlook Self-efficacy Scale was specifically designed for this study to address a significant gap in the ability of existing standardised questionnaires to evaluate the outcomes targeted by this intervention. The authors’ wanted to use a singe questionnaire that assessed participants’ confidence in their knowledge, skills and abilities pertaining to the physical, social and emotional aspects of life with HIV. Confidence in ability to disclose HIV and to use risk reduction strategies within intimate relationships in particular, are not assessed in any current standardised assessments. This scale is comprised of 19 questions which are broken down into five individual dimensions including knowledge, communication, relationships, social participation and emotions. The primary researcher (TM) composed the scale based on existing chronic condition self-efficacy scales [58]. Questions were developed targeting the specific aims of the Positive Outlook Program. The contributing authors then further refined the questionnaire. Minor adjustments were made to the scale following piloting by the research team and two HIV positive peer support officers. As this is a new scale, validity and reliability of data using this scale cannot be assured. Results obtained from this scale will therefore be interpreted and reported with caution.

#### Secondary outcome measures

##### 

**Health related quality of life: Short-Form Health Survey Volume 2 (SF-12v2^®^)** The SF-12^®^ consists of eight subscales including: physical functioning, role limitations due to physical health problems, bodily pain, social functioning, general mental health, role limitations due to emotional problems, vitality and general health perceptions [59]. The psychometric properties have been tested and proved sound amongst a variety of general and disease specific populations (reliability coefficient median 0.76; relative validity median = 0.97) [59]. It is also considered a valid measure for use with PLHIV [60].

##### 

**Depression Anxiety and Stress: Depression Anxiety and Stress Scale (DASS)** The DASS is a 21-item standardised self-report measure consisting of three scales measuring depression, anxiety and stress. In a large clinical sample (N = 437) the DASS demonstrated high levels of internal consistency (alpha = 0.96, 0.89 and 0.93) for depression, anxiety and stress respectively [61].

##### 

**Social Support: Duke Social Support Index (DSSI)** The 11-item DSSI was derived from the longer, 35-item DSSI and consists of a subjective evaluation of the adequacy of support received as well as a more objective evaluation of type and number of social interactions [62]. Goodger and colleagues [62] conducted a study evaluating the reliability and validity of the scale in a sample of 565 community dwelling people aged 70 years and over. They reported that the scale demonstrated good internal consistency (alpha. = 0.77), and test-retest reliability (n = 117) from 0.07 to 0.81.

##### 

**Domain specific adjustment: Mental Adjustment to HIV Scale (MAH)** The MAH scale is based on the Mental Adjustment to Cancer (MAC) scale [63] which has demonstrated validity and reliability in a range of cancer populations [64]. Ross and colleagues [65] reported on the use of the MAH in a population of 107 Australian men with HIV. They reported that the five subscales of the MAH demonstrated adequate Cronbach’s alpha reliabilities between 0.55 and 0.8 [65].

#### Statistical analysis

Descriptive statistics will be used to characterise the sample at baseline. Unpaired t-tests and chi-square tests will detect any differences between the control and intervention groups at baseline. Analysis of covariance (ANCOVA) will be used to evaluate changes in the dependent variables at post-test and follow up, controlling for differences between the groups at baseline. Data analysis will use an intention-to-treat approach. All analyses will be conducted using SPSS for Windows.

#### Qualitative data

Case studies of 12 men from the intervention groups will be conducted to explore in depth, the experiences of participating in the program. The sample will be composed of three men from each intervention group. Sampling of participants for the case studies will be purposive, with the aim to obtain a range of successful and unsuccessful outcomes as measured by the assessment battery. Data collection will involve semi-structured interviews conducted via telephone completed within one week of program completion. Semi-structured interviews will also be conducted with each facilitator involved in the delivery of the Positive Outlook program. Interviews will be digitally recorded and transcribed verbatim. Data will be de-identified and analyzed using the constant comparative method of qualitative data analysis [66]. The primary researcher will also keep field notes for the duration of the RCT.

#### Process evaluation

Process evaluation will consist of a mixed methods approach using both quantitative and qualitative data as recommended for process evaluation of RCT’s [67]. Website data (number of logins; duration of logins; pages visited; modules completed; discussion board posts and attendance at live chats per participant) will be used to evaluate participation and adherence to the program. At the conclusion of the program, participants will be asked to complete an evaluation survey regarding their experiences using the Positive Outlook Program. Questions will include outlining the strengths and weaknesses of the program; suggestions for improvement; satisfaction with the website; level of participation in the program and overall satisfaction with the program. Participant and facilitator interviews as described above will also contribute to process evaluation.

### Trial organisation and management

The proposed study will be conducted in accordance with the ethics guidelines as explained in the National Statement on Ethical Conduct in Human Research [68]. Ethics approval has been granted by the Human Research Ethics Committee at Monash University, Edith Cowan University, The Alfred Hospital, ACON and the Victorian AIDS Council. The trial has been registered with the Australia and New Zealand Clinical Trial Registry #00362515.

### Trial status

No data cleaning or analysis of the RCT has been executed prior to submission of this manuscript.

## Discussion

We describe here the design of the Positive Outlook study, a randomised controlled trial evaluating the effectiveness of an online self-management program for gay, homosexual and other MSM living with HIV. The intervention is based on self-efficacy theory and uses a self-management approach to enhance participants’ confidence, skills and abilities to manage many of the psychosocial issues associated with living with HIV.

This study is significant for several reasons. Meeting the health care needs of individuals with HIV is an important public health issue. The Australian Government is strongly committed to the self-management of chronic conditions, listing self-management support as a key component of routine care [69]. Self-management requires changes to the physical, emotional and social aspects of ones life [17]. Due to significant advances in the effectiveness of ART, the physical effects of HIV are relatively well managed by medications. In contrast, more investment is required to address the psychological and social issues that continue to impact the lives of people living with HIV. For example, issues surrounding stigma, negotiating intimate relationships and disclosure are, in many ways, unique to the experience of living with HIV and thus require targeted attention in order to be adequately addressed and managed [20,39,70].

Existing self-management interventions for PLHIV have addressed adherence to medications, medication side-effects and symptom management, physical exercise, nutrition, stress, anxiety and self-efficacy [71-77]. Findings from a recent systematic review of self-management education programs for PLHIV indicated that, while such programs may result in short-term improvements in physical, psychosocial, health knowledge and behavioral outcomes, further research needs to be devoted towards establishing the effectiveness of programs improving social support, the management of HIV within intimate relationships and quality of life [39].

To our knowledge, in Australia, the only available self-management program for PLHIV is the Stanford program (Positive Self Management Program) [53], offered through the Bobby Goldsmith foundation in Sydney. This program is more general in its approach and an evaluation of the program noted its focus on improving participants self efficacy, which can result in group roles being forced upon participants and little attention being given to participants’ own issues because they do not fit within with the syllabus [70]. The program is not presently offered online, limiting access for people who may encounter barriers to participation, including stigma, time, geographical location and transport.

Other programs available in Australia utilizing self-management elements, such as life coaching and peer support, are currently available through various community organizations supporting PLHIV. However, the majority of these groups are targeted towards, and accessed by, those newly diagnosed. Given the prominence of psychosocial issues for PLHIV, particularly regarding disclosure and negotiating intimate relationships, it is clearly important that these issues be addressed to enhance the quality of life of PLHIV in Australia.

The model of care for PLHIV has long been based on one of empowerment, encouraging patients to take an active and informed role in their health care. Gay men have been widely recognized as advocates for their health and community in their response to HIV. In dealing with the HIV epidemic, gay men have developed a strong sense of agency and lead the way in forming partnerships with health care providers, advocating for one’s self and adopting a ‘peer support’ model of care [78]. Peer support and education programs have been widely used for PLHIV [78]. Benefits of peer support include the low cost of implementation and the general accessibility and availability as opposed to care provided by health care professionals. The shared experiences, circumstances and common characteristics amongst peers further facilitates their appeal and effectiveness [78].

The present intervention specifically targets the five priority areas identified in the needs assessment: (1) Managing the emotional impact of HIV (2) Disclosing HIV status to family and friends (3) Maintaining social connectedness (4) Managing HIV within intimate relationships (5) Disclosure of HIV status to intimate partners. The two pilot studies assisted the intervention team to further develop and refine the program in order to maximize participants’ engagement and satisfaction with the program. The main changes included the addition of the ‘Live Chat’ component and a reduced focus on the Action Planning Activities.

The most recent National HIV Strategy (2010–2013) called for a reduction in the “transmission of and morbidity and mortality caused by HIV and to minimize the personal and social impact of HIV” [79]. In recognition of their commitment to achieving the overall goal and priority actions identified in this strategy, community organizations across Australia are well positioned to adopt and promote an online self-management style program in order to improve the QOL of PLHIV.

